***Null Hypothesis***

There is no difference in the length of time that virus persists in body fluids or between individuals or in relation to antibody response or HIV status.

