***1.2.1 Main objective***

To analyze EBOV persistence in body fluids (semen or vaginal secretions/breast milk/rectal swabs/saliva/sweat/urine/tears) in relation to antibody response in serum.

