***2.2.1 Follow-up procedures***

**Main study**

The EVD survivors with at least one of the body fluid positive at RT-PCR will be asked to return for follow-up study visits, first time after two weeks then every two to four weeks until there have been two consecutive negative RT-PCR test results for each body fluid. Participants will be asked to continue follow-up until all body fluid specimens are negative for two consecutive visits.

Lactating women will receive their results within 3 days after the collection of the specimen. Women with positive results in breast-milk will be offered testing every 3 days till 2 consecutive tests are negative; women with a first negative test will come back after 3 days to do a confirmatory test.

Menstruating women will be asked to provide a specimen as close to the first day of their period as possible, and a second specimen before the end of the period. Menstrual blood sampling may be done at the same time as other body fluid testing, or may occur after testing of other body fluids has been completed.

Women will be offered pregnancy testing at every visit, and if positive they will be referred to ANC, pending on gestational age and needs, care will be offered in line with national guidelines for Ebola survivors. Pregnant women will be offered participation in the study.

Pregnant women will have an additional follow up questionnaire to record the outcome of delivery, which will occur if a pregnant woman delivers before she has completed the study follow up, or if the delivery takes place after body fluid testing has finished. A special questionnaire to record the pregnancy and delivery outcomes will be completed by the healthcare personnel providing ANC.

Breast-feeding women who test positive for EVD in breastmilk will be offered free formula feeding in line with current WHO guidelines.

A study card ID check will be done for each participant coming for a follow-up visit. If the participant has lost his/her study ID card, the locked in ID code may be accessed, if participant’s identity can be verified.

At each visit, participants will be informed of their RT-PCR Ebola test results (if available) including negative results. HIV testing will be offered at each visit. A follow-up questionnaire will be administered, including sexual behavior over the last two weeks since the previous visit, see Annex 1.

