**7. Data analysis plan**

• Descriptive analysis of the study participants will be performed by the study PI and staff with the support of WHO and US-CDC. WHO and US-CDC technical assistance may be provided as needed for these and any additional analyses of the study data. Any further statistical analysis will be conducted using adequate statistical program packages with the assistance of WHO and US-CDC.

• Viral Persistence time will be measured in days or months from time after symptom onset and will also be presented as time after ETU discharge.

• The primary measures of interest are:

o the period prevalence of viral persistence in 1st/baseline samples (0-3 months, >3-6 months etc)

o survival probabilities over time (based on base-line positive samples)

o maximum duration of tissue culture-positive results for EBOV by number of days since symptom onset for each of the various body fluid specimen types.

• EBOV presence, measured both as detected RNA and isolated virus, in any of the relevant body fluids, will be analyzed in relation to time of persistence.

• Analysis of RNA derived from selected specimens collected during the study will include genetic analysis and comparison with Ebola virus sequences derived from the participant. This will include sequences characterized during the acute phase of EVD (if available) and comparison with other Ebola virus sequences that have already been characterized. This will help to better describe the variation in virus sequence over time within individuals.

• Viral persistence in a body fluid at a certain period in time, will be analyzed in relation to host factors such as age, sex, co-morbidity including HIV and its clinical characteristics, severity of the earlier Ebola infection and Ebola sequelae, as well as presence and titers of IgM and IgG antibodies in serum. Information on exposure to experimental treatment or vaccination will also be taken into account in the analysis.

• Participant information on sexual history will be analyzed for frequency and type of

(protected/unprotected/vaginal/oral/anal) sex.

• The calculation of correlation between positive RT-PCR and culture tests for each body fluid specimen types will be performed, conditioned upon time since the first convalescent negative RT-PCR blood test.

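### The hypothesis concerns how long virus persists, but host factors and antibody titers are linked only to persistence within a period; for semen, a time-to-clearance regression should be added

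*Combined protocol and SAP*

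**What the plan says.** The main objective (section 1.2.1) is "To analyze EBOV persistence in body fluids" and, in the same sentence, "in relation to antibody response in serum". The null hypothesis (section 1.2) is on the duration scale: "There is no difference in the length of time that virus persists in body fluids or between individuals or in relation to antibody response", and it goes on to name HIV status.

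The Data analysis plan (section 7) has one bullet that names host factors: "Viral persistence in a body fluid at a certain period in time, will be analyzed in relation to host factors such as age, sex, co-morbidity". Antibodies come in the same bullet: "as well as presence and titers of IgM and IgG antibodies in serum". It names no outcome coding, model, test or effect measure.

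Section 7 also lists time-based measures: "survival probabilities over time (based on base-line positive samples", the maximum duration of culture positivity, and virus presence in relation to persistence time. None mentions a host factor. The specific objectives (section 1.2.4) likewise list the survival function and the host factors as separate items. The host-factor objective there is not confined to a period.

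The data would support more. Under Follow-up procedures (section 2.2.1), participants with a positive fluid return "first time after two weeks then every two to four weeks until there have been two consecutive negative RT-PCR test results for each body fluid". Blood for antibody testing is drawn at the same visits (section 2, Main study).

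**The concern.** The question is about duration and the schedule observes duration, but the one analysis meant to explain differences between survivors is framed around a period. In section 7 the only periods spelled out are the windows for first-sample prevalence (0-3 months, over 3 to 6 months).

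The target stratum is 0-3 months from symptom onset, while the Background reports RT-PCR-positive semen at 9 months. If most men are still positive in the first window whatever their antibody level, status in that window says little about who clears sooner. A real association with antibody response could then be missed on the study's main objective. The results are intended to inform counseling messages and recommendations (section 14).

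**Working it through.** **The plan's own figure.** The only sample-size figures are upper bounds for zero positives: 1 - 0.025^(1/N) gives 7.1%, 3.6%, 1.8% and 1.2% for N = 50, 100, 200 and 300, matching the plan. They concern fluids other than semen. No power, effect size or alpha is stated for any host-factor comparison, so there is no planned power to reproduce.

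**Closed-form comparison for semen.** From the documents: 120 men (60 at each of two sites), entry 0-3 months after onset. Assumed: a binary factor split 60/60, entry uniform over the window, exponential clearance with overall median m, clearance hazard ratio (HR) 2 split symmetrically, two-sided alpha 0.05, and every baseline positive followed to clearance.

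- Hazards: (ln 2/m) × √2 and (ln 2/m)/√2.
- Proportion positive at baseline: p = (1 - e^(-3λ))/(3λ).
- Period status: two-proportion test of p between groups.
- Clearance time in baseline positives: power = Φ(√(D·a(1-a)) · ln 2 - 1.96), where D = 60(p₁ + p₂) and a is one group's share of D.

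Worked for m = 4 months: λ = 0.245 and 0.123, so p = 0.71 and 0.84.

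- Status: the pooled standard error is 0.0765 and the unpooled 0.0756. Power = Φ((0.129 - 1.96 × 0.0765)/0.0756) = 39%.
- Clearance time: D = 93 and a = 0.54. Power = Φ(√(93 × 0.54 × 0.46) × 0.693 - 1.96) = 91%.

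| Median (months) | Status, HR 2 | Clearance time, HR 2 | Status, HR 1.5 | Clearance time, HR 1.5 |
|---|---|---|---|---|
| 1 | 61% | 67% | 26% | 30% |
| 2 | 55% | 84% | 23% | 41% |
| 4 | 39% | 91% | 16% | 50% |
| 6 | 30% | 93% | 13% | 53% |

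**Simulation with interval censoring.** In the likelihood, a man negative at entry E contributes 1 - S(E), one who clears between L and U contributes S(L) - S(U), and one never seen to clear contributes S(L).

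- 120 men, exponential clearance, 2-weekly visits, HR 2, medians 2/4/6 months (150 runs, standard error up to 4 points): status 50/39/27%; status adjusted for time since onset 55/43/33%; regression on all men 93/95/94%.
- 100 men, Weibull clearance (shape 1.5), entry 1-3 months, 20% drop-out, HR 2, medians 3/5/7 months (400 runs): baseline status adjusted for day 50/30/24%; status at one well-chosen later time 68/67/61%; regression 92/90/82%. Separate code with 300 runs gave 54/28/22%, 71/66/66% and 91/87/84%.
- 50 men, same design: 24/14/14%, 41/36/36% and 66/65/54%.

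**Where the gain shrinks** (100 men, median 5 months, HR 2).

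- Entry at 1-6 months: 48% baseline status, 73% best single time, 86% regression.
- Log-normal data fitted with a Weibull model: 43% status, 70% regression.
- 20% of men never positive: 15% and 68%; with log-normal data as well, 16% and 44%.

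With no effect, the regression rejected in 4-8% of runs in the 300- and 400-run checks, so an inflated error rate does not explain the gap.

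**Other fluids.** With 240 participants and prevalence of 1-5% there are 2 to 12 positives. Power at HR 2 is 7-22% by either route, so there is no gain.

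**The case against.** A reader might infer that the plan tests host factors against a yes/no status and discards the clearance times. The documents do not support either. Section 7 says only that the relation will be analyzed, and it does not attach the prevalence windows to the host-factor bullet. Clearance times are used: survival probabilities and maximum duration are primary measures. They are simply not related to host factors.

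It is also fair to say that this is a descriptive cohort sized on a zero-prevalence bound. It claims no power for host factors and leaves further analysis open. The power figures are therefore not a loss against a promised figure. They compare two ways of using the same data under assumed inputs, with a fixed binary factor in place of a titer.

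Three technical objections stand and shape the fix.

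- Treating baseline negatives as left-censored assumes that every man once shed virus in semen.
- For those men, titer is measured after clearance.
- The protocol allows for intermittent shedding and tests for re-positivity at 3 and 6 months, which a single clearance time does not describe.

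Relating titer to shedding status within a period is also a defensible question, so the bullet should be kept and added to.

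What the objection does not remove is that no sentence in the plan relates host factors or titers to the length of persistence, which is what the null hypothesis is about.

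**Conclusion.** The point holds as a mismatch between hypothesis and analysis, and it matters in practice for semen. If host factors are related only to baseline-period status, power at a hazard ratio of 2 with 100 to 120 men is roughly 20-55%. Interval-censored regression reaches roughly 80-95% at medians of 2 to 7 months. Against the more generous reading, status at one well-chosen later time, the gain in the 100-man design is 21 to 24 points (68/67/61% against 92/90/82%), falling to 13 points if entry extends to 6 months.

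These sizes rest on an assumed clearance distribution, hazard ratio and factor split, none of which the documents give. The advantage is small at a 1-month median (61% against 67% using baseline positives only). It narrows under misspecification or a never-positive fraction, and it is absent for fluids near zero prevalence. This is a recommended improvement to the analysis plan and does not invalidate the design.

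**What to change.** Add to the host-factor bullet in section 7, for semen and any other fluid with enough positives:

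- **Main host-factor analysis:** regression of time from symptom onset to RT-PCR clearance on host factors (Weibull or log-normal), reporting the hazard or time ratio with a 95% CI.
- **Clearance:** the first of two consecutive negatives, with later re-positivity described separately.
- **Censoring:** baseline negatives left-censored at entry; those who clear interval-censored between last positive and first confirmed negative; all others right-censored at last positive.
- **Titer:** enters as the baseline value, adjusted for time since onset.
- **Sensitivity analysis:** baseline positives only, conditioning on being positive at entry. This covers never-positive men and titers measured after clearance.
- **Period status by host factor:** keep as descriptive, and as the only analysis for fluids with almost no positives.

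The cost is plan wording, a standard interval-censored model and slightly more analysis work, with no new visits, specimens or participants. The downside is a distributional assumption, which should be checked against a Turnbull curve.

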More recently a Scottish nurse experienced a severe complication with meningitis where Ebola virus detected in the cerebrospinal fluid and blood approximately 10 months after recovering from the initial infection. This raised questions on the frequency of this event among the population of survivors, and whether virus persisting in the body could be detected intemittently. These questions have to be better documented for the population of Ebola survivors in the three countries.

Many questions remain on how to manage pregnancy and delivery in Ebola survivors. Pregnant women who develop EVD have many complications, which include high mortality and stillbirths. In a few cases, a miscarriage occurred after a woman had resolved EVD infection in the blood, and the fetus and amniotic fluid was found to have virus. Little is known about whether virus can persist in women who have recovered from EVD and became pregnant after recovery.

*Ebola survivors in Sierra Leone*

The current situation for Ebola survivors in Sierra Leone involves several survivors’ support groups, actively working to provide risk reductioncounseling and support of various qualities to survivors.

In addition, survivors’ clinics are available, which provide medical care for post-Ebola sequelae, together with counseling, including around sexual transmission. The survivors are provided job opportunities in different organizations for community engagement to educate on stigma of sexual transmission; social mobilization and contact tracing. These activities are run in collaboration with UNICEF and the national survivors’ association.

The situation in the recent past has been that male survivors were being locked up, shunned and stigmatized by the community, and some chiefs also suggested that male survivors should be jailed in order to prevent sexual transmission of EVD. Upon actions from the National Ebola response committee, the attorney general wrote a letter officially condemning the persecution of male survivors. Nevertheless, male survivors are especially keen on the outcome of this study to know when it is safe to be intimate with their partners.

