***Sub-objectives***

- To assess concordance between RT-PCR test results and virus isolation test results
- To characterize the genetic sequence of virus detected in body fluid specimens over time
- To assess the frequency of sequelae and severe complications at 3 and 6 months following two negative test results
- To assess if virus is detectable at long time intervals (3 and 6 months) following two negative test results
- To describe outcomes of pregnancy and delivery in pregnant participants

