Titers of EBOV-specific IgG and IgM antibodies in blood will be analyzed by means of serology, at the field laboratory (Chinese-CDC in Jui). Blood for antibody analysis will be collected at the same time as body fluid specimens, and will hence be discontinued when the survivor has had two EBOV RT-PCR negative body fluid specimens from each fluid sampled.

At each visit, trained counselors will provide specific risk reduction counseling on the prevention of transmission of EBOV. Participants will be offered HIV testing and will receive counseling if they elect to be tested. All detected HIV positive patients will be referred to national HIV services if not already on antiretroviral treatment. A sufficient quantity of condoms will be offered at each visit. If needed, participants will be referred to clinical survivor services. Women will be offered pregnancy testing, and if positive they will be referred to ANC, pending on gestational age and needs, care will be offered in line with national guidelines for Ebola survivors. Pregnancy is not an exclusion criteria for this study.

Pilot and main study participants will be offered a follow-up visit with a questionnaire and body fluid testing at 3 and 6 months after their second negative RT-PCR test result. During the follow-up visits, a questionnaire asking about health events that occurred since their last study visit will be given, and body fluid specimens will be collected (for the pilot, semen specimens; for the main study, venous blood, semen or vaginal/menstrual blood as appropriate, rectal swab, sweat, urine, saliva, tears, and breast milk if applicable. If all body fluid specimens test negative, no further testing will be performed until the next scheduled 3 or 6 month visit. If a body fluid specimen tests positive, follow-up testing will be performed every 2 weeks until 2 consecutive negative specimens test results are obtained.

Pregnant women will be offered a special follow-up to monitor their pregnancy and delivery outcomes and the follow-up is detailed in Annex 3 “Ebola Viral Persistence study: Nested Pregnancy cohort study - VPNP”.

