**2.1 Procedures**

***2.1.1 Study site selection***

The MoHS and the Ministry of Social Welfare, Gender and Children's Affairs (MSWGCA) identified four potential study sites in three high burden districts (Western Area, Bombali, and Port Loko). To enable recruitment of recent survivors from districts with ongoing transmission, Freetown is identified as a suitable recruitment area, and the possibility of a 2nd site is under investigation. Preliminary information suggests that survivors treated in Kenema during the early phase of the epidemic may also be residents of Port Loko, since no ETU was established there initially.

The pilot study has been conducted at M34 in Freetown. The main study will continue at M34 in Freetown.

In addition the possibility to start up a 2nd study site is being investigated. Guiding principles for selection of a 2nd site are feasibility in terms of construction and staffing and availability to invite more recent survivors, as well as tail-end long term male survivors. Lungi Government Hospital, as well as other options such as expansion within the MoD network of health posts, are currently explored.

The study sites will be the setting for all initial and follow-up visits of survivor participants and the location for interviews, specimen collection, and risk reduction counseling regarding test results. Study participants will be referred to HIV and survivor services within the hospitals where the study sites are located.

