Participants will be asked to continue providing specimens of each body fluid and venous blood at every study visit until they have had two consecutive negative test results for that body fluid. Participants whose body fluids all have been RT-PCR negative at two consecutive study visits will exit from the study cohort.

For participants that have had two consecutive negative test results, a follow-up visit to administer a questionnaire and body fluid testing will be scheduled at 3 and 6 months after the last 2nd negative body fluid specimen has been collected. The same body fluids would be collected as in the initial visits, and the questionnaire will focus on health events and status since the last follow-up visit.

Interviews will take place in a designated private room at the study clinic.

A time to come back to the clinic for follow-up will be booked and agreed upon at each preceding visit. Contact information will be reviewed at each visit and reminder calls will be made if applicable. Study participants will be supported to fulfill their participation in the study by counseling offered at each visit together with assistance with referrals to clinical care as needed. Carefully timed reminder calls will be made to participants who have missed their appointments, and flexibility will be provided in terms of appointment bookings and any needs for additional counseling or information.

Renumeration for participation will be paid at each visit.

The participant will be offered test results from the preceding visits and offered counselling on transmission risks targeted to lab findings according to a standardized counseling script (Annex 2).

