• ETU CRFs will be accessed retrospectively to investigate clinical severity of disease and so on. Currently we do not know what the quality of the data in the ETU CRFs will be, as they have not been accessed. Where ETU records do exist for study participants, there may be inconsistency in the data collected between the ETU CRFs and the study questionnaires. The ETU CRFs will primarily be used to add additional information that the participant may not have been able to recall; and verify data that has been collected in the corresponding section of the questionnaire. In cases where there are discrepancies with what is recorded in the questionnaire and the ETU CRFs, additional weight will be given to data captured in the questionnaire. The data capture for the study questionnaires is conducted by designated, trained team members and is therefore standardised. Data collected in ETU CRFs is likely to have varied between ETUs and is likely to have been collected in a less uniform way (unknown amount of training of staff, likely to have been collected by a large pool of staff and so on.

- 3 and 6 month visit body fluid RT-PCR test results will be analyzed to describe if body fluid specimens can test positive after two consecutive negative test results. A descriptive analysis of the questionnaire will be performed to assess any clinical complaints or health events, and to compare them to previous test results for any correlation of complications related to previously detected virus persistence.
- Outcomes of pregnancy will be described and related to the participant’s previous test results.

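### Severe complications at 3 and 6 months are counted only among people who attend the visit, so deaths and participants never reached are missed and the frequency is likely understated

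*Combined protocol and SAP*

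**What the plan says.** The objective is a frequency. The sub-objectives under section 1.2.1 include: "To assess the frequency of sequelae and severe complications at 3 and 6 months following two negative test results". Section 1.1 gives the motive, a survivor with meningitis and virus in spinal fluid and blood about 10 months after recovery, and adds: "This raised questions on the frequency of this event among the population of survivors".

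The data come from attended visits. Under Main study in section 2, pilot and main study participants "will be offered a follow-up visit with a questionnaire and body fluid testing at 3 and 6 months", and at those visits "a questionnaire asking about health events that occurred since their last study visit will be given". Section 2.2.1 sets the entry condition: "For participants that have had two consecutive negative test results, a follow-up visit to administer a questionnaire and body fluid testing will be scheduled". Section 2.1.1 fixes the place: "The study sites will be the setting for all initial and follow-up visits of survivor participants".

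For absences, section 2.2.1 says: "Carefully timed reminder calls will be made to participants who have missed their appointments". It also allows flexible rebooking. Section 7 describes the analysis in one line: "A descriptive analysis of the questionnaire will be performed to assess any clinical complaints or health events". It adds a comparison of complications with earlier test results. It states no denominator and no rule for missed visits.

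**The concern.** Whether a participant is counted depends on attending, and attending depends partly on the outcome. A participant who has died cannot complete a self-report questionnaire, and one who stays seriously ill may never come back to the clinic. The event that prompted this objective is of that severe kind.

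The results are meant to update counselling messages and recommendations (section 14). A low or zero frequency among attenders could be read as reassurance about all survivors when it describes only those well enough to come.

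**Working it through.** **Is there another source?** I looked for anything in the document that would capture a severe event without attendance.

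- Case report forms from the Ebola treatment units (section 7) concern the earlier acute illness.
- Referral to survivor services (section 2, Main study) has no described return of data.
- The one form completed by outside providers (section 2.2.1) covers pregnancy and delivery only.
- The discontinuation criteria (section 2.2.2) mention neither death nor loss to follow-up.
- Section 12.4 allows people who repeatedly fail to complete visits to be dropped.

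None fills the gap.

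**Inputs.** The plan states no expected complication frequency, attendance rate or precision target for this objective, so there is no figure to reproduce. The only attrition figure is the 20% drop-out allowance under Sample size calculations: 50 × 1.20 = 60 per sex per site, which matches the stated 60. Retaining 50 of 60 means a share d = 10/60 = 16.7% not seen. Applying this to the 3- and 6-month visits is my assumption. The recent-survivor cohort is 60 × 2 sexes × 2 sites = 240. The risk ratio RR of non-attenders to attenders is also assumed, over 0.5 to 10.

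**Bias formula.** If attenders have risk p and non-attenders RR × p, the true frequency is p[(1 − d) + d × RR]. The attender-only frequency as a share of the true one is therefore 1/[(1 − d) + d × RR].

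| d | RR 0.5 | RR 1 | RR 2 | RR 5 | RR 10 |
|---|---|---|---|---|---|
| 5% | 1.03 | 1.00 | 0.95 | 0.83 | 0.69 |
| 16.7% | 1.09 | 1.00 | 0.86 | 0.60 | 0.40 |
| 30% | 1.18 | 1.00 | 0.77 | 0.45 | 0.27 |

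For example, at d = 1/6 and RR = 5: 1/(5/6 + 5/6) = 0.60. The share does not depend on the number enrolled, so adding the PLHIV sub-cohort or the pilot men does not change it.

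**Illustration (assumed counts).** Of 240 due, 200 attend and 4 report a severe complication: 4/200 = 2.0% (exact 95% CI 0.5% to 5.0%).

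- RR 2: (4 + 0.04 × 40)/240 = 2.3%
- RR 5: (4 + 0.10 × 40)/240 = 3.3%
- RR 10: (4 + 0.20 × 40)/240 = 5.0%
- Bounds: 4/240 = 1.7% if no non-attender had an event, 44/240 = 18.3% if all did

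If 0 of 200 report one, the attender-only interval is 0 to 1.8%, but the upper bound for all 240 is 40/240 = 16.7%.

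**Association with earlier persistence.** Suppose attendance has probability a1 for people with a complication and a0 for those without, whatever their earlier persistence. With true cell counts A and B (complication yes, no) among those with persistence, and C and D among those without, the attenders' odds ratio is (a1·A × a0·D)/(a0·B × a1·C) = AD/BC. It is unchanged; what is lost is precision.

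**The case against.** A reader might infer that everyone who is ill or in hospital when a visit falls due is lost. The documents do not support that. The questionnaire looks back to the last study visit, there are two visits, and missed ones are rebooked. Someone admitted at month 3 who recovers can report it late or at month 6. The lasting loss is deaths, people still too ill at the end, and people never reached.

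A reader might also infer that the link between complications and earlier persistence is distorted in the same way. Attendance that depends on the outcome alone does not do this. Bias would need attendance to depend on earlier persistence as well, and nothing in the documents shows that.

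It would also go too far to say that the reminder calls do not record outcomes. The protocol is silent, and the questionnaires and the Operations Manual with its procedures are separate documents that I have not seen. What stands is that the protocol and analysis plan commit to no tracing.

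The direction is not certain either. Visits bring payment and referral to care, so people with complaints may be more willing to come, and healthy non-attenders would partly offset the loss. If non-attenders had half the risk, the frequency would be overstated by about 9% at the assumed attendance.

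Finally, this is a descriptive sub-objective, and the three primary measures in section 7 are virological and unaffected. That limits the weight of the point. It does not supply the missing denominator or a way to record deaths.

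**Conclusion.** The point holds for deaths, for participants who stay too ill to attend and for those never reached. As written, the plan has no means of counting them, and the frequency of severe complications is likely understated.

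The documents do not allow the size to be computed. On the assumption that 50 of 60 attend, attenders would show 0.86, 0.60 or 0.40 of the true frequency at risk ratios of 2, 5 or 10. The understatement disappears at a ratio of 1 and reverses below it.

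People who die or are lost before two negative results are also outside the count, but the wording of the sub-objective sets that limit. For the comparison with earlier persistence, the expected loss is mainly of precision.

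**What to change.** In section 2.2.1, state that for each missed 3- or 6-month visit the planned call will record vital status, any hospital admission since the last visit and the reason for absence. A call to the participant cannot establish that participant's death, so allow contact with a proxy, or tracing by the community liaison officers (section 4.1), when the participant cannot be reached. Neither route may disclose study results or HIV status, in line with sections 6 and 12.

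In section 7, state that deaths and admissions count as severe complications. State also that the frequency is reported among all participants due for the visit, across the main study, the PLHIV sub-cohort and the pilot. Show the numbers attended, traced and unknown, and give bounds treating the unknowns as non-events and then as events.

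The cost is modest: contact details are already kept and reviewed, the calls are planned and the liaison officers are on staff. What is added is a short record for each missed visit, proxy contact details and staff time for tracing. Calls and proxies give less detail than a visit, and the bounds stay wide if many remain unknown.
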